#### Piloting and Evaluating the PrEP US NoW Intervention

The primary outcomes from the trial will include feasibility and acceptability, improvement in social capital, and reduction in internalized homonegativity. Secondary outcomes will include estimates of intervention efficacy in increasing PrEP uptake and decreasing condomless anal sex acts. Figure 4 outlines the study design for the pilot intervention.

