#### Intervention Arm

A total of 6 young, Black, sexual minority men's social networks, each including 5 young, Black, sexual minority men (including index participants) and 1 Black female facilitator, will participate in the intervention arm. Before the trainings, the Black female facilitators completed a baseline survey electronically, which measured sociodemographics, HIV knowledge, PrEP knowledge, HIV-related stigma [53], homophobia [54], and PrEP stigma. Black female facilitators have completed their training on app usage. In addition, Black females also completed an (web-based or face-to-face) intensive training covering (1 day) cultural competence and humility when working with sexual and gender minority populations; experiences of stigma among young, Black, sexual minority men in the South; LGBTQ-focused sexual health topics; and basic information about HIV treatment and prevention, including the use of PrEP and steps required to engage in PrEP care.

All young, Black, sexual minority men in the intervention arm will also receive a training (web-based or face-to-face), including a tour of the downloadable US NoW app, a brief demonstration of how to join and participate in the web-based discussion, and practice on posting content publicly and privately. Once trained, young, Black, sexual minority men will complete HIV testing using OraQuick rapid HIV test (remote participants will be asked to text a picture of the test result via a secure server) and an electronic baseline survey prior to study commencement capturing information on sociodemographics, stigma related to race or ethnicity and sexual practices or orientation [55,56], HIV, poverty, PrEP use [57], PrEP knowledge [57], sexual history and practices [58], alcohol [59] and substance abuse [60], and depression [61] and anxiety [62], using appropriate validated measures. In the event an individual tests positive on an HIV test, they will be referred to the linkage team at the study site’s university-affiliated clinic for counseling, access to confirmatory testing, and linkage to care, if necessary.

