Following enrollment of young, Black, sexual minority men and Black women facilitators, 4 predesignated 60-minute discussions with the network and the Black woman facilitator will commence. Activities of Black female facilitators will include leading discussions and answering any questions or comments posted by young, Black, sexual minority men. Young, Black, sexual minority men participants will be instructed how to use the app throughout the 4-week period. The importance of attendance at the discussions will be emphasized and incentivized through app badges given by other members within the network and by Black female facilitators. Additionally, a reminder, through phone texts, will be sent to young, Black, sexual minority men participants about discussion times.

The data collection began in August 2024 and is expected to be completed in December 2025. Once the intervention ends, young, Black, sexual minority men participants will receive follow-up surveys electronically at *T*_1_ (1-month postintervention) and *T*_3_ (3-month postintervention), capturing the primary and secondary outcomes (explained in detail later). Young, Black, sexual minority men will also be asked to perform a rapid HIV OraQuick test at *T*_3_, remotely. Similarly, Black female facilitators will also complete a follow-up electronic survey at *T*_1,_ which will measure feasibility and acceptability, as well as any changes in stigma and PrEP knowledge or attitudes from baseline. In addition to surveys, Black female facilitators will also participate in web-based qualitative interviews at *T*_3_, which will evaluate PrEP knowledge, intersectional stigma, and change in attitudes following the intervention and gain descriptive information about the process (ie, feasibility and acceptability) of PrEP US NoW facilitation. Additionally, experiences and comfort around delivering the intervention will also be assessed.

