##### Primary Outcomes

Four primary outcomes—feasibility, acceptability, social capital, and homophobia—will be measured. *Feasibility* and *acceptability* will be measured using responses from *T*_3_ surveys. Validated scales will include the Acceptability of Intervention Measure, Intervention Appropriateness Measure, and Feasibility of Intervention Measure [63]. These scales include straightforward questions such as “[PrEP US NoW] is appealing to me,” to which participants respond on a 5-point Likert scale. Feasibility will also be measured by monitoring in-app usage characterized by the completion of 15-minute discussions, the number of posts, and the total time spent in virtual discussions. Moreover, intervention fidelity will be monitored by documenting the completion of 15-minute discussions and the response rate for questions posted, and by reviewing the accuracy of information shared. *Social capital* will be measured using a modified version of Chen’s Personal Social Capital, the Modified Social Capital Scale [64], adapted for young, Black, sexual minority men use. This scale measures bonding (resources accessed within similar sociodemographic social groups) and bridging (resources derived from cross-identity connections) social capital with sources and types of support (eg, emotional, instrumental, and informational). *Homophobia* will be measured using the Internalized Homophobia Scale [65].

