### Data Analysis

The data will be stored in a secure server housed in the health system at the University of Alabama at Birmingham and will only be viewed on designated encrypted devices by the principal investigator and study team. Descriptive statistics will be calculated to characterize acceptability and feasibility measures. Stratifying young, Black, sexual minority men by age ranges, 18-21 and 22-29 years, all outcomes will be described by independent variables using frequencies (percentages). Generalized estimated equations will be used to perform logistic regression with empirical standard errors using an exchangeable working correlation, based on the reasonable assumption of equal correlation among members within each index. Other structures will be examined. These models will be used to estimate the rate of PrEP uptake to determine the difference in odds of PrEP uptake, controlling for within-index correlation to determine the difference in the odds of uptake between the two groups (intervention and control). Separate models will be fitted directly after the intervention (*T*_1_) and 3 months following the intervention (*T*_3_). For each model, independent predictor variables (sociodemographic factors, variables related to stigma, knowledge, sexual history and practices, alcohol and substance abuse, and depression and anxiety) will be included as covariates. All categorical outcomes (advancement, change in social capital, connectedness, and condomless anal intercourse in the past 3 months) will be treated similarly. Lastly, if there are overlaps in social networks between index cases, we will perform a network analysis to determine closeness, betweenness, and degree to determine if there will be potential for treatment interference.

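### Change in social capital and connectedness, both scale scores, are classed as categorical and sent to logistic GEE with no category defined; internalized homophobia, a primary outcome, is left out of the modelled outcomes; and none of the three scales is listed at baseline

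*Protocol article*

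**What the plan says.** All references are to the protocol article.

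- **Outcomes as aims** (Piloting and Evaluating the PrEP US NoW Intervention), as the article frames them: "The primary outcomes from the trial will include feasibility and acceptability, improvement in social capital, and reduction in internalized homonegativity".
- **Outcomes as measures** (Primary Outcomes): "Four primary outcomes—feasibility, acceptability, social capital, and homophobia—will be measured". Social capital uses the Modified Social Capital Scale: "This scale measures bonding (resources accessed within similar sociodemographic social groups) and bridging (resources derived from cross-identity connections) social capital". Homophobia uses the Internalized Homophobia Scale. No cut-point is given for either.
- **Secondary Outcomes**: connectedness to one's ethnic community is measured by an adapted scale, condomless anal intercourse in the past 3 months is labelled ordinal, and PrEP uptake is yes or no.
- **Data Analysis**: logistic regression by GEE with an exchangeable working correlation is set out for PrEP uptake, with separate models at T1 and T3. Then: "All categorical outcomes (advancement, change in social capital, connectedness, and condomless anal intercourse in the past 3 months) will be treated similarly". Feasibility and acceptability get descriptive statistics. All outcomes are also to be described by frequencies and percentages.
- **Baseline** (Intervention Arm): the men complete "an electronic baseline survey prior to study commencement capturing information on sociodemographics, stigma related to race or ethnicity and sexual practices or orientation", followed by HIV, poverty, PrEP use and knowledge, sexual history, alcohol and substance use, depression and anxiety. The T1 and T3 surveys are described as "capturing the primary and secondary outcomes (explained in detail later").

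**The concern.** A score built from a multi-item scale carries graded information. Logistic regression needs categories, so the score must first be cut, and the article does not say where. Cutting discards information, and leaving the cut-point open lets it be chosen after the data are seen. The Sample Size Justification says that what matters in this pilot is feasibility and the precision of estimated changes for designing later studies, so lost precision goes directly against its purpose.

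Internalized homophobia is one of four primary outcomes. Two of the other three, feasibility and acceptability, are expressly descriptive. The third, social capital, is modelled, as are two secondary outcomes besides PrEP uptake. Homophobia receives only the general sentence on frequencies and percentages.

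The aims are also phrased as "improvement in social capital, and reduction in internalized homonegativity", which presupposes a starting value. If the scales were not asked at baseline, neither within-person change nor adjustment for the starting score is possible, and a missing pre-intervention score cannot be recovered later.

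**Working it through.** **1. The plan's own figures.** The article gives 95% CI margins only for two binary rates: ±12% and ±25% for 50% advancement, and ±9% and ±18% for 15% PrEP uptake, at within-index correlation 0 and 0.9. Take a margin of 1.96·√(p(1−p)·D/N) with D = 1 + (5−1)·ICC and N = 60 in 12 clusters of 5. The second value applies the bootstrap factor √(11/12).

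| p | ICC | Wald margin | With √(11/12) | Stated |
|---|---|---|---|---|
| 0.50 | 0 | 12.7% | 12.1% | 12% |
| 0.50 | 0.9 | 27.1% | 26.0% | 25% |
| 0.15 | 0 | 9.0% | 8.7% | 9% |
| 0.15 | 0.9 | 19.4% | 18.6% | 18% |

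With the bootstrap factor, each stated figure is matched to within about one point when all 60 men are used. None of them gives the precision for social capital, homophobia or connectedness, so the article has no figure of its own for these scales.

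**2. Outcome against stated analysis.**

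| Outcome | Role | Measure | Stated between-arm analysis |
|---|---|---|---|
| Social capital | primary | scale | logistic GEE, as categorical change |
| Internalized homophobia | primary | scale | none named |
| Feasibility, acceptability | primary | scales, app use | descriptive only |
| Connectedness | secondary | scale | logistic GEE, as categorical |
| Condomless anal intercourse | secondary | ordinal | logistic GEE, as categorical |
| PrEP uptake | secondary | yes/no | logistic GEE |

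Only PrEP uptake clearly suits the model as described. Among the primary outcomes, social capital is the only one sent to it.

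**3. What a split would cost (illustrative).** Assumptions: normal score with SD 1, cut at the median, 30 men per arm in clusters of 5, follow-up scores only.

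- Relative efficiency = 2/π = 0.637. CI widening = 1/√0.637 = 1.25.
- Half-width for a difference in means = 1.96·√(2D/30), with D as above.

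| ICC (assumed) | D | Continuous score | After median split (×1.25) |
|---|---|---|---|
| 0 | 1.0 | 0.51 SD | 0.63 SD |
| 0.1 | 1.4 | 0.60 SD | 0.75 SD |
| 0.3 | 2.2 | 0.75 SD | 0.94 SD |

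**4. What baseline adjustment would gain (illustrative).** Residual individual-level variance is 1 − ρ², where ρ is the correlation between baseline and follow-up. At assumed ρ of 0.3, 0.5 and 0.7 this is 0.91, 0.75 and 0.51. The article gives no value for ρ.

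**5. Baseline list against the change outcomes.** The list in Intervention Arm carries its own measure references and includes stigma related to sexual orientation, but under different references from the Internalized Homophobia Scale. It names neither that scale nor the social capital or connectedness scale. The aims, the Sample Size Justification and Data Analysis all speak of improvement, reduction or change. The two sets of statements need to be reconciled. In addition, the covariates named for the models do not include a baseline value of the outcome.

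**The case against.** **A reader might infer that the scales were not collected at baseline.** The documents do not establish this. The baseline list is one sentence in a condensed article and does not claim to be complete. The Independent Variables section names no time point. A planned change in social capital, and the three surveys (baseline, T1, T3) in Ethical Considerations, both point towards a baseline measurement. What stands is that the scales are not listed and that this fits poorly with the change outcomes.

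**A reader might infer that the intervention effect cannot be estimated.** It can. Networks are randomized through their index men, so T1 and T3 scores can be compared between arms without a baseline. Baseline scores would still help: only 12 indexes are randomized, the arms are unblinded, and the Figure 4 legend places the referral of control network members after randomization.

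**A reader might turn 0.64 into a loss of 22 of the 60 men** (60 × 0.363 ≈ 22). That presumes a median split, which the article never states, and treats clustered men as independent. The efficiency figure shows only the kind of cost involved. The article also does not say that the ordinal outcome will be collapsed to two levels; it leaves the handling open.

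**The method for homophobia may sit in an analysis plan that is not shown.** This is a fair point, and it makes that omission the smaller part of the concern. It does not answer the classification of social capital and connectedness as categorical, which this document does state.

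**This is a pilot.** That is also true, but precision is one of its stated purposes.

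**Conclusion.** The point holds in a limited form. One primary and one secondary scale outcome are classed as categorical and assigned to logistic GEE without a defined category, and an ordinal outcome is sent to the same model. A second primary outcome, internalized homophobia, has no named between-arm model. Continuous analysis adjusted for baseline is more precise and costs little.

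The size depends on choices that the article does not make. Under a median split of a normal score, the CI would be about 25% wider. Baseline adjustment would remove 9% to 49% of individual-level variance at assumed correlations of 0.3 to 0.7.

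On baseline, the supported conclusion is an inconsistency to resolve: the scales are not listed, while change, improvement and reduction are planned. If they are in fact missing, within-person change and baseline adjustment are lost, but the between-arm comparison at T1 and T3 is not.

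**What to change.** 1. Analyse social capital, internalized homophobia and connectedness as continuous scores at T1 and T3, using an identity-link GEE or a linear mixed model with arm and baseline score and allowance for index clustering. Report mean differences with confidence intervals.
2. Add internalized homophobia to the list of modelled outcomes.
3. Use an ordinal (cumulative-logit) model for condomless anal intercourse.
4. Remove the two scales from the categorical list. If a categorical version is wanted as well, define the category in advance and keep it supplementary.
5. Confirm that the three scales are in the baseline survey and say so. If they are not, add them for men not yet surveyed. The article's Results section reports that baseline surveys were still ongoing, so this step is the time-sensitive one.

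**Cost.** Steps 1 to 4 change analysis wording only. Step 5 adds at most a few survey items, and men already surveyed may have missing baseline scores that the analysis must handle. With 60 men, sparse ordinal categories may need merging by a rule set beforehand.

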#### Recruitment, Screening, and Consent

A network-based approach was used to identify social network members of the index young, Black, sexual minority men participants by following a sociogram protocol [52], that is, graphic plotting of the young, Black, sexual minority men’s social network members. The recruitment for young, Black, sexual minority men is still ongoing, whereas recruitment for Black female group facilitators has been completed. For each index young, Black, sexual minority man in the intervention arm, a Black female social network member, referred by the CAB and external to the young, Black, sexual minority men's network, was screened. The inclusion criteria for the Black women facilitators included (1) self-identified Black race and female gender, (2) age >18 years, and (3) fluency in written and spoken English. The goal was to have at least one eligible Black female member per 6 eligible young, Black, sexual minority men, serving as a facilitator in each group. The ultimate Black female facilitator selection only consisted of cisgender women and was made by the CAB based on a structured interview to assess stigmatizing beliefs and cultural humility. As this was an egocentric network analysis, the investigators assumed networks were independent of one another; however, the first name and last initial of participants were collected to evaluate for overlaps across networks in the analyses.

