##### Sample Size Justification

For this pilot study, the importance of sample size lies in establishing feasibility and the precision of estimated changes, which will inform the design of future studies. Twelve index participants will be recruited, and each index will provide information to recruit 4 others, yielding a total sample size of 60. Six indexes will be randomized to PrEP US NoW and 6 to the control group. The clustering of participants within the index (specifically the PrEP US NoW group) may result in a reduced effective sample size. Assuming no correlation within indices for all participants, a rate of advancement of 50% for PrEP US NoW, the bootstrap 95% CI would have a margin of error of ±12%. On the other hand, assuming a large correlation, 0.9, the margin of error becomes ±25%. With an anticipated 15% PrEP uptake, the 95% CI margin of error is ±9% for no correlation and ±18% for a correlation of 0.9.

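### Closeness, betweenness and degree ignore trial arm, so the planned interference check cannot tell overlap within an arm from overlap between arms

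*Protocol article*

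**What the plan says.** The section on recruitment, screening and consent states that "the investigators assumed networks were independent of one another". It adds that "the first name and last initial of participants were collected to evaluate for overlaps across networks in the analyses". Overlap is thus foreseen, and some data are collected to find it.

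The Data Analysis section gives the consequence: "if there are overlaps in social networks between index cases, we will perform a network analysis". That analysis is to "determine closeness, betweenness, and degree to determine if there will be potential for treatment interference". Trial arm is not mentioned at this point.

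The outcome model is a logistic GEE with an exchangeable working correlation and empirical standard errors, described as "controlling for within-index correlation to determine the difference in the odds of uptake between the two groups (intervention and control"). The index is the only clustering unit. The section says that other categorical outcomes, including change in social capital, will be handled in the same way.

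On allocation, the Sample Size Justification says "Six indexes will be randomized to PrEP US NoW and 6 to the control group", and that "each index will provide information to recruit 4 others, yielding a total sample size of 60".

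**The concern.** Interference between arms arises when a man in a control network is tied to a man in an intervention network. Closeness, betweenness and degree describe a man's position in the graph. A control man with four ties to other controls has the same degree as one with four ties to intervention men. Betweenness may flag a man who bridges two networks, but not whether those networks are in different arms. So the tool does not answer the question it is given.

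The question matters in this trial for two reasons.

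- The intervention is meant to act through network ties, so a cross-arm tie is a plausible route by which its content reaches controls. If the intervention works, that pulls the difference between arms towards zero, for PrEP uptake (secondary) and for social capital (primary).
- Some overlap is plausible. Index men for the trial are recruited with resources similar to those of the interview phase: a contact list from earlier studies, listservs, venues, and recruiters with large community followings. Each index then brings in men he knows.

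The pilot's estimates are meant to inform the design of a later trial. Unrecognized dilution would carry into that planning, and the amount of cross-arm overlap is itself useful feasibility information for a network-randomized design.

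**Working it through.** The article gives no figure for overlap or interference, so there is none to reproduce. Three checks were made.

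**1. Do the named measures respond to arm?**

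Inputs: 60 men and 12 networks of 5, with 6 networks per arm (Sample Size Justification). Assumed for illustration: all five men in a network know each other, and two ties join different networks (network 1 with 2, and network 3 with 4). The graph is held fixed and only the arm labels change.

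- Degree of a bridging man: 4 ties inside his network + 1 outside = 5.
- Betweenness of a bridging man: he lies on the paths from 4 network mates to 5 men in the linked network, 4 × 5 = 20.
- Closeness of a bridging man, scaled for a disconnected graph: he reaches 9 men at a total distance of 5 × 1 + 4 × 2 = 13, so (9/13) × (9/59) = 0.106.

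| Quantity | Both ties within an arm | Both ties across arms |
|---|---|---|
| Maximum degree | 5 | 5 |
| Maximum betweenness | 20 | 20 |
| Maximum closeness | 0.106 | 0.106 |
| Cross-arm ties | 0 | 2 |
| Control men tied to an intervention man | 0 | 2 |

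The three centralities are the same for every man in both columns. Only the arm-aware counts differ.

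**2. If two networks overlap, how often would they be in different arms?**

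With 6 and 6 networks there are 12 × 11 / 2 = 66 pairs, of which 6 × 6 = 36 are cross-arm: 36/66 = 55%. The recruitment section also gives a 2:1 ratio, which does not match 6 and 6. With 8 and 4 the share would be 32/66 = 48%. Either way, an overlap between a random pair is about as likely to cross arms as not.

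**3. How large could dilution be?**

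Assumptions, none of them stated in the article as arm-specific rates: 15% uptake in unexposed controls (the article's anticipated uptake, which it does not tie to an arm), 35% in the intervention arm, and a share *f* of controls who take up PrEP at the full intervention rate because of a cross-arm tie.

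Control uptake = 0.15 + *f* × (0.35 − 0.15). Observed difference = 0.20 × (1 − *f*).

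| *f* | Control uptake | Difference (points) | Odds ratio |
|---|---|---|---|
| 0 | 15% | 20 | 3.05 |
| 10% | 17% | 18 | 2.63 |
| 20% | 19% | 16 | 2.30 |
| 30% | 21% | 14 | 2.03 |

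With 30 control men, these shares are 3, 6 and 9 men. For scale, the article's margin of error at 15% uptake is ±9% with no correlation and ±18% with a correlation of 0.9. The simple formula with all 60 men gives 1.96 × √(0.15 × 0.85 / 60) = ±9.0%. With a design effect of 1 + 4 × 0.9 = 4.6 it gives ±19.4%, close to the stated bootstrap figure.

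**The case against.** The strongest reply is that overlap is not ignored. Names are collected to find it, the Figure 4 caption has control-arm referrals undergo sociograms, and overlap between indexes is what triggers the network analysis. Each index's arm is known, so a cross-arm overlap can be read from these data. A reader might infer that contamination would go unmeasured and that linked networks would go unnoticed. The documents do not support that. What is missing is narrower: the named measures do not sort overlap by arm, and the article does not say that anything else will.

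A second reply is that a rule for handling overlap may sit in the full protocol or analysis plan, which is not shown. That stands, so the absence of a stated consequence is not held against the article here. It does not repair the choice of measures, which the article does state.

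Third, the size is easily overstated.

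- The intervention is four discussions led by a trained facilitator in a modified app. A tie to a participant does not deliver that, so full transfer of effect is an upper bound.
- In the illustration the loss is 2 to 6 points, smaller than the article's own margins for a single proportion, in a pilot sized for feasibility and precision.
- A reader might also infer that every linked pair of networks costs one of the 12 independent clusters. That is not so in general. One shared tie does not make two networks of five fully dependent, and three mutually linked networks form three pairs but merge into one unit, a loss of two.

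Finally, two tempting remedies do not hold up. Dropping only control men with cross-arm ties would remove better-connected men from one arm, and the article itself links social capital to network size and diversity. Checking for overlap before allocation conflicts with the Figure 4 caption, which places randomization before referral and sociograms.

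**Conclusion.** The concern holds in a limited form. Closeness, betweenness and degree are functions of the graph alone, so they cannot separate overlap within an arm from overlap that links control men to intervention men. That is a stated method that does not fit its stated purpose, and it needs no assumption about how much overlap occurs. The GEE, as described, allows for correlation within an index and not for ties between indexes.

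The effect on the results cannot be sized from the documents. The 2-to-6-point dilution rests on assumed uptake of 15% and 35%, on 10% to 30% of controls being exposed, and on full transfer of the effect. It is a ceiling for those inputs and not an expectation. In a 60-man pilot with PrEP uptake as a secondary outcome this is a cheap improvement. It does not undermine the trial.

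**What to change.** In the Data Analysis section, replace the three centralities, or supplement them, with an arm-aware count:

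- For each man, count the ties to men in the opposite arm, by matching sociogram nominations and participant names across networks.
- Do the matching before the data are deidentified for analysis. First name and last initial can match wrongly, so check apparent matches against the other contact methods to be obtained from participants. Nominated men who never enrol may remain unresolved, and their number should be reported.
- Report, by arm, the number of men and of networks with any cross-arm tie.
- Add one sensitivity analysis in which linked networks form a single cluster in the GEE. This is a conservative limit, since linked networks need not be fully dependent.
- Add one exploratory analysis that leaves out men with cross-arm ties from both arms. It selects on connectedness and should be read with that in mind.
- Label any dilution figure as an assumed upper bound.

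The cost is a little more analysis on data the trial already collects, and an earlier slot for the name matching. The sensitivity estimates will be less precise, because they rest on fewer men or fewer clusters. Allocation, recruitment and the main model need not change.
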